### Blinding and study termination

This study will be an open label study that only the assessing optometrist and ophthalmologist will not be aware of the participant allocation and the participants, external observer responsible for participant allocation, and the physician performing the intervention will be aware of the patient allocation.

### Concealment

We will be using sealed envelopes for concealment.

### Sample size

Given the pilot nature of the study, no formal sample size calculation was conducted. However, the results will be used to estimate effect sizes and variability to inform future definitive trials. we will include 10 patients in each group of the study. This number was also determined based on available resources, expected recruitment rates, and the exploratory aim of generating effect size estimates for planning a future definitive trial. Since the number of mustard gas veterans are limited, we will be using each patient of this group as their own controls.

### Statistical analysis

All statistical analyses will be performed using Stata version 17.0. The analysis will focus on estimation rather than formal hypothesis testing, in line with the pilot nature of this trial. The primary goal is to generate effect size estimates and their corresponding 95% confidence intervals to inform the design of a future definitive trial. A p-value of < 0.05 will not be interpreted as definitive evidence of a treatment effect due to the small sample size.

Descriptive statistics will be used to summarize baseline characteristics of participants across the three groups. Continuous variables will be reported as mean ± standard deviation (SD), and categorical variables will be expressed as frequencies and percentages.

To estimate the effect of the intervention in group A vs. B comparison, regression-based modeling will be employed. For continuous outcomes, a linear regression model will be used. The β coefficient will represent the adjusted mean difference in the outcome between the HUCB and conventional treatment groups. Its 95% confidence interval will provide a range of plausible effect sizes. For binary outcomes, a logistic regression model will be used. The exponentiated coefficient for the treatment group will be reported as an Odds Ratio (OR) with its 95% confidence interval.

For Group C, which uses a paired-eye design, a linear mixed-effects model will be used to account for the non-independence of two eyes from the same patient. The model will include treatment (HUCB vs. conventional) as a fixed effect and a random intercept for each patient. The primary output will be the estimated mean difference between treatments and its 95% confidence interval.

The effect size and standard deviation of the OSDI score (primary outcome) will be used to inform future sample size and power calculations for a definitive randomized controlled trial. The 95% confidence intervals obtained in this pilot will provide the parameters required to estimate the sample size needed to detect a clinically meaningful difference in OSDI between treatment groups with adequate power.

All analyses will follow the intention-to-treat principle. Efforts will be made to minimize missing data by maintaining regular contact with participants and performing reminder calls before each visit. In case of missing outcome data, multiple imputation using chained equations will be applied if more than 10% of data are missing for the primary outcome (OSDI score). The imputation model will include treatment group, baseline OSDI score, and other relevant covariates.

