**Materials and methods:**

This pilot randomized controlled trial will evaluate the efficacy of HUCB eye drops in three patient groups: (A) Sjögren’s patients treated with HUCB drops, (B) Sjögren’s patients receiving conventional treatment, and (C) mustard gas veterans receiving conventional treatment in the right eye and HUCB drops in the left eye. Patients will be assessed using subjective and objective tools, including the Ocular Surface Disease Index (OSDI), visual acuity, tear film breakup time (TBUT), SM tube test, and fluorescein staining based on SICCA criteria. Group allocation will follow a blocked randomization sequence for groups A and B; group C will follow a within-subject paired-eye design. Follow-up will occur at 30 and 60 days.

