### Randomization

A randomized list with block size of 2 will be generated using the Sealed Envelope website [26]. The sequence of participants in the list will be available only to an external observer responsible for participant allocation, that will not participate in the other parts of the study. The randomization will be performed only for groups A and B. Patients in group C will get conventional treatment in their right eyes and umbilical cord serum in their left eye.

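### Cheap improvement: the Group C model lists no eye-level baseline, visit or eye term, and the A vs B model names neither its adjusting covariate nor the visit at which OSDI is read

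*Protocol article*

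**What the plan says.** All references are to the protocol article.

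- **Group C, Statistical analysis.** A linear mixed-effects model is planned because two eyes of one patient are not independent. Its terms are given: "The model will include treatment (HUCB vs. conventional) as a fixed effect and a random intercept for each patient". No baseline value, visit or eye-within-patient term is listed.
- **Group C allocation, Intervention and Randomization.** Eyes are not randomised. The right eye gets conventional treatment and the left eye serum in every patient.
- **A vs B, Statistical analysis.** "For continuous outcomes, a linear regression model will be used", and "The β coefficient will represent the adjusted mean difference in the outcome between the HUCB and conventional treatment groups". The covariates behind the adjustment are not named.
- **Visits.** "Follow-up will occur at 30 and 60 days" (Abstract). Table 1 schedules OSDI and the eye measures at screening, Day 30 and Day 60. Neither follow-up day is named as the one at which the OSDI effect is read.
- **Baseline elsewhere.** Baseline OSDI is named only for the imputation model, which is used if more than 10% of OSDI data are missing.
- **Size and purpose.** "we will include 10 patients in each group of the study"; "no formal sample size calculation was conducted". "The primary goal is to generate effect size estimates and their corresponding 95% confidence intervals", to inform a definitive trial.

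**The concern.** The trial's product is an effect size and its 95% interval, so the terms of the effect model matter more here than any test.

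In Group C treatment is tied to the side. The patient intercept takes out how severe a patient is overall, but not whether the left eye started better or worse than the right. Such a difference is indistinguishable from a treatment effect unless the eye's own baseline is used. Two follow-up visits also leave open whether the coefficient refers to Day 30, Day 60 or their average. If both visits go into one model with only a patient intercept, the two readings of one eye count as independent given the patient, and the interval becomes too narrow.

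In A vs B, calling the estimate adjusted without naming baseline leaves a potential gain in precision to chance. An unnamed visit leaves more than one candidate for the OSDI effect that is meant to plan the next trial.

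**Working it through.** The plan gives no power, effect size or SD, so there is no figure of its own to reproduce. The inputs from the protocol are 10 patients per group, two follow-up visits, 95% intervals, 1:1 randomisation for A vs B ("A randomized list with block size of 2 will be generated") and fixed sides in Group C. The baseline-to-follow-up correlation r and the Group C variance components are assumptions. All results are in SD units.

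**A vs B, 10 per arm**

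- Without baseline, the half-width is t(18) × √(2/10) = 2.101 × 0.447 = 0.940.
- With baseline as covariate, the expected half-width is about t(17) × √[(2/10)(1 − r²)(1 + 1/16)], with t(17) = 2.110.

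| assumed r | half-width with baseline | against 0.940 |
|---|---|---|
| 0 | 0.973 | 4% wider |
| 0.2 | 0.953 | 1% wider |
| 0.5 | 0.842 | 10% narrower |
| 0.7 | 0.695 | 26% narrower |

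- Break-even on variance is (1 − r²)(17/16) = 1, so r = √(1/17) = 0.24. On half-width, allowing for the change in t, it is 0.26. Call it about 0.25.
- The SE of a chance baseline difference is √(2/10) = 0.447, so a difference above 0.5 SD arises in about 26% of such trials. At r = 0.5 a difference of exactly 0.5 SD moves an unadjusted estimate by 0.5 × 0.5 = 0.25 SD. This is sampling error that a valid interval already allows for.

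**Group C, 10 patients, two eyes, no true effect**

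Three assumed variance splits were used, written patient/eye/residual, each summing to 1.

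*A left-right difference of 0.5 SD that persists from baseline.* Without eye-level baseline all of it enters the estimate (simulated 0.50 in each split). Regressing the Day 60 between-eye difference on the baseline between-eye difference has expected slope eye/(eye + residual), so the remainder is 0.5 × (1 − slope):

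- 0.5/0.3/0.2: slope 0.6, remainder 0.20
- 0.6/0.2/0.2: slope 0.5, remainder 0.25
- 0.5/0.1/0.4: slope 0.2, remainder 0.40

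The simulation of 20,000 trials gave 0.20, 0.25 and 0.40. These figures belong to this within-patient form of the adjustment.

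*SE of the Day 60 contrast with no left-right difference, without and then with baseline adjustment.* 0.318 to 0.269; 0.283 to 0.260; 0.315 to 0.330, in the same order. The last split, with weak eye persistence, loses slightly. Analysed at Day 60 alone, the listed terms amount to a paired comparison and coverage was 95%.

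*Days 30 and 60 stacked with treatment and patient intercept only.*

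- True SE = √[2(eye + residual/2)/10].
- The model's SE is about √(s²/10). Here s² pools 9 between-eye degrees of freedom, with mean square 2 × eye + residual, and 20 within-eye degrees of freedom, with mean square equal to the residual.
- For 0.5/0.3/0.2: s² = (9 × 0.8 + 20 × 0.2)/29 = 0.386, so the model SE is 0.197 against a true 0.283.

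| split | true SE | model SE | simulated coverage |
|---|---|---|---|
| 0.5/0.3/0.2 | 0.283 | 0.197 | 81% |
| 0.6/0.2/0.2 | 0.245 | 0.180 | 84% |
| 0.5/0.1/0.4 | 0.245 | 0.215 | 90% |

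The coverage uses the quantile 1.96. Using t with 29 degrees of freedom on the same SEs adds only about one to two percentage points, so the cause is the missing eye-level term.

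**The case against.** The strongest reply is that a condensed article commonly leaves covariate lists to a fuller document, and that saying a model will include two terms does not exclude others. For A vs B most of this stands. The coefficient is called adjusted, so a reader who infers that A vs B will be unadjusted goes beyond the text. What remains there is an unnamed covariate and an unnamed visit, and the precision figures apply only if baseline is left out. For Group C the reply is weaker: the article chose to state the model's terms, and as listed they do not fit two visits or a fixed side.

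Other objections also hold:

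- Chance imbalance between A and B is not bias, because those groups are randomised.
- The gain depends on a correlation that the protocol does not give. Entry limits on TBUT, SM tube and staining (Eligibility criteria) restrict the baseline range of those outcomes and may lower it.
- A reader might infer that the Group C effect will be diluted because screening values are stacked with follow-up values. No section plans to enter baseline as an outcome row.
- With complete data, leaving out visit does not itself bias the treatment contrast. The harm is an undefined time point and, if visits are stacked, a misstated interval.
- Fixed sides are a design matter that no covariate fully repairs.

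**Conclusion.** The point holds as a cheap improvement to the analysis wording. It is strongest in Group C. Followed as listed, the model passes a persistent left-right difference into the estimate in full: 0.5 SD if that is its size, against 0.20 to 0.40 SD after adjustment. If both visits are stacked, it gives intervals with about 81% to 90% coverage. Both results rest on assumed variance components, and the first also on an assumed left-right difference; the protocol does not show that one exists. The coverage loss arises only if the visits are stacked.

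For A vs B the point is one of naming. Leaving baseline out would cost about 10% of half-width to be gained at r = 0.5 and 26% at r = 0.7, and nothing below about r = 0.25. The unnamed OSDI visit matters because that effect size is meant to feed the next trial's sample size.

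**What to change.** **A vs B.** State that each outcome is adjusted for its own baseline value. Name one primary visit for OSDI, for example Day 60 as the last visit, and make the other secondary.

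**Group C, outcomes recorded per eye.** Add that eye's baseline value. Then do one of two things:

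- analyse one named primary visit, keeping treatment and the patient intercept; or
- model both visits with visit, treatment-by-visit and an eye-within-patient random effect, and report the contrast at the named visit.

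State also that baseline adjustment only partly removes a left-right difference.

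**Cost.** No new data: Table 1 already schedules the baseline values. A vs B loses one degree of freedom. Group C gains one fixed term with a single visit, or three fixed terms and one variance component if both visits are modelled. Where the baseline correlation or eye persistence is weak, precision falls slightly: half-width from 0.940 to at most 0.973 SD in A vs B, and SE from 0.315 to 0.330 in one assumed Group C case.

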## Discussion

This randomized controlled trial aims to evaluate the efficacy of human umbilical cord blood (HUCB) serum eye drops in improving ocular surface health, restoring vision, and alleviating severe dry eye symptoms in patients with Sjogren’s syndrome and chemical warfare veterans. By incorporating both subjective and objective outcome measures, this study will provide a comprehensive assessment of HUCB eye drops’ therapeutic potential.

The novelty of this study lies in its investigation of HUCB eye drops as a regenerative treatment for severe dry eye, particularly in patients with underlying autoimmune and chemically induced ocular surface damage. Unlike conventional treatments, HUCB serum eye drops offer essential growth factors, neurotrophic components, and antimicrobial agents that closely mimic natural tears, potentially promoting ocular surface repair and regeneration more effectively.

One of the strengths of this study is its randomized and controlled design, which includes validated assessment tools, a well-defined patient population, and a structured follow-up protocol. The inclusion of both Sjogren’s syndrome patients and chemical warfare veterans broadens the applicability of the findings, with potential implications for other severe ocular surface disorders, such as Stevens-Johnson syndrome and industrial chemical exposure injuries.

This study is open-label because the physical properties and storage conditions of umbilical cord blood serum differ visibly from conventional artificial tears, making participant blinding infeasible. However, the ophthalmologist and optometrist responsible for clinical assessments will remain blinded to treatment allocation to minimize measurement bias. Furthermore, objective ophthalmic parameters (TBUT, fluorescein staining, SM tube test) are included as secondary outcomes to complement the subjective OSDI score. The absence of participant blinding is acknowledged as a limitation, and results based on subjective measures will be interpreted with caution. Although a longer follow-up period would provide valuable information about the durability of treatment effects, this pilot study was designed primarily to assess short-term feasibility and preliminary efficacy. Due to resource and logistical constraints, extending follow-up beyond 60 days was not possible. The results of this trial will, however, inform the design and timing of follow-up assessments in a future larger-scale RCT with a longer observation period.

In conclusion, this study has the potential to advance treatment options for patients with severe dry eye and ocular surface damage. If successful, the findings may support the integration of HUCB serum eye drops into clinical practice as a safe and effective alternative for managing complex ocular surface diseases.
